#### Other explorative outcomes

The gut microbiota composition and functional profiles of donors and recipients in relation to (non-) response will be assessed using shotgun metagenomic sequencing. Strain tracking will be employed to determine donor-derived strain engraftment. Gut microbial-derived metabolites will be analysed using untargeted and targeted approaches, such as high-performance liquid chromatography-mass spectrometry, to measure metabolites involved in cell signalling, with a particular focus on SCFAs and tryptophan. Changes in yeast composition and growth will be assessed through culture techniques. The intestinal immune cell profile in relation to clinical outcomes will be analysed using cytometry by time-of-flight on colon biopsies. Luminex multiplex technology will be performed on supernatants from processed biopsies to assess changes in cytokine and chemokine profiles.^35^ Habitual dietary intake will be obtained by a semiquantitative questionnaire, the Groningen IBD Nutritional Questionnaire (GINQ)^36^ and a 3-day food diary. We will explore associations between the habitual diets of participants (both donors and patients) and clinical outcome. Health-related quality of life will be measured with the SF-36 questionnaire,^37^ and fatigue will be assessed with the Functional Assessment of Chronic Illness Therapy-Fatigue questionnaire.^38^ Other outcomes include changes in the mucosal transcriptome.

### Sample size calculation

At the time of writing the initial protocol, four RCTs^9^,^12^ had been published on FMT for inducing remission in UC, including our previous FMT trial (TURN).^9^ In the TURN trial, the primary endpoint was reached in 30% of patients, with a placebo response rate of 20%.^9^ The other three published RCTs had efficacy rates ranging from 24 to 32% and placebo rates from 5% to 9%.^9^,^12^ In the current study, we aim to augment the treatment effect by selecting faeces donors on their microbiota profile, using anoxic processing, and by promoting engraftment through dual-route administration and repeated FMTs. We therewith estimate to boost the treatment effect to 33–40%. By using a more stringent endpoint, we anticipate a lower placebo compared with the TURN trial, aligning with rates observed in other studies.

The sample size calculation was performed using nQuery software (Cork, Ireland) with the following assumptions: efficacy in the placebo group of 10%, efficacy in the treatment group of 37%, two-sided significance level (α) of 0.05 and desired power of 80% (β=0.20). Based on these parameters, a sample size of 38 patients per group, totalling 76 patients, is required. The study incorporates an adaptive design that allows for an increase in the sample size up to a maximum of 100 patients to account for (early) drop-outs (online supplemental table 6).

### Recruitment

Patients are recruited from the outpatient clinics of the Amsterdam UMC and UMCG by their treating gastroenterologist. Additionally, patients from other hospitals in the Netherlands can be referred to the Amsterdam UMC by their treating gastroenterologist or general practitioner. To inform patients and healthcare practitioners about the trial, recruitment efforts include advertisements on the Amsterdam UMC intranet webpage, a general webpage and Google Ads, a dedicated Facebook page and through the Dutch Maag Lever Darm Stichting.

### Patient allocation and blinding

Randomisation is performed using a computerised random-number generator within the Electronic Data Capture system Castor, allocating patients in a 1:1 ratio to either allogenic (donor) FMT or autologous FMT. Randomly permuted blocks of 2, 4 or 6 are applied with no additional stratification. A research assistant conducts the randomisation and subsequently prepares autologous FMT or collects syringes with donor FMT (based on Epstein-Barr virus and Cytomegalovirus matching), according to the allocation outcome.

To ensure blinding, FMT syringes are visually and olfactorily concealed in capped syringes covered with aluminium foil and labelled identically for autologous and donor FMT. All labels include a tearable section with the allocation and a unique code. A second independent research assistant verifies either the preparation of autologous FMT or the correct matching of donor syringes and removes the tearable labels, which are maintained in a drug accountability log. The research assistants are the only individuals who are unblinded and have no further role during the study. FMT administration and all visits are conducted by a blinded research nurse or fellow. Gastroenterologists performing sigmoidoscopies and treating physicians are also blinded.

De-blinding of investigators may occur after all patients have reached the primary endpoint (week 8), to facilitate data publication. Patients who do not meet the secondary endpoint of clinical response at week 8 and who have an endoscopic Mayo subscore of ≥2 at week 8 can be unblinded if they wish to continue with open-label extension. Open-label extension with donor FMT will only be available to patients who were originally allocated to autologous FMT.

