#### Secondary outcomes

Secondary outcomes include:

Proportion of patients with:Clinical response per adapted Mayo score at week 8 (ie, excluding Physician’s Global Assessment (PGA) subscore): a decrease from baseline ≥2 points and ≥30%, plus a decrease in RBS≥1 or an absolute RBS≤1.Clinical improvement per partial adapted Mayo score at week 8 (ie, excluding PGA and endoscopy subscore): a decrease from baseline ≥1 points and ≥30%, plus a decrease in RBS≥1 or an absolute RBS≤1.Full clinical remission per full Mayo score at week 8: a decrease from baseline of ≤2 points with no subscore >1.Complete remission per full Mayo score at week 8: ≤2 points reduction from baseline with no subscore >1 and a rectal bleeding score and endoscopic subscore of 0.Sustained steroid-free remission per adapted Mayo at week 8; SFS≤1, RBS=0, endoscopic subscore≤1 and no need for rescue therapy until week 52.Endoscopic complete remission at week 8: endoscopic subscore=0.Endoscopic improvement at week 8: endoscopic subscore of 0 or 1.Endoscopic response at week 8: ≥1 point reduction in summed endoscopic Mayo score (endoscopic subscore of rectum+endoscopic subscore of sigmoid).Histological remission assessed via Nancy Histological Index (NHI)^32^,^34^: NHI≤1.Change in:Simple Clinical Colitis Activity Index from baseline to week 1, 2, 3, 4, 8, 18, 39 and 52.Partial Mayo: from baseline to week 1, 2, 3, 4, 8, 18, 39 and 52.IBD-Control: from baseline to week 2, 4, 8, 18, 39 and 52.Occurrence of AEs

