### Trial status

Recruitment of faeces donors started in December 2018. The first study patient was included in June 2020. Recruitment was completed in November 2024, and the follow-up period will continue until January 2026.

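### Investigators may be de-blinded once all patients pass week 8, while week 18 to 52 secondary outcomes are still being collected in late enrollees, and the protocol does not say who stays blinded

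*Protocol article*

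**What the plan says.** All places are in the protocol article.

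- **Patient allocation and blinding, the release:** "De-blinding of investigators may occur after all patients have reached the primary endpoint (week 8), to facilitate data publication". The trigger is study-wide, the wording is permissive, and the group released is named only as investigators.
- **Patient allocation and blinding, who is blinded:** "FMT administration and all visits are conducted by a blinded research nurse or fellow", and "Gastroenterologists performing sigmoidoscopies and treating physicians are also blinded". Neither sentence gives an end date. Separately, patients without clinical response at week 8 and with an endoscopic subscore of 2 or more may be unblinded individually if they want the open-label extension.
- **Secondary outcomes, scores after week 8:** "Partial Mayo: from baseline to week 1, 2, 3, 4, 8, 18, 39 and 52" and "Simple Clinical Colitis Activity Index from baseline to week 1, 2, 3, 4, 8, 18, 39 and 52". IBD-Control is also scheduled at weeks 18, 39 and 52.
- **Secondary outcomes, sustained remission:** "Sustained steroid-free remission per adapted Mayo at week 8; SFS≤1, RBS=0, endoscopic subscore≤1 and no need for rescue therapy until week 52".
- **Statistical methods:** p-values of secondary outcomes are Holm-Bonferroni adjusted, so these outcomes are tested and not merely described.
- **Trial status:** the first patient was included in June 2020, recruitment was completed in November 2024, and "the follow-up period will continue until January 2026".

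**The concern.** The trial is described as double-blind, and its one-year follow-up is listed as a strength. The release rule lets investigators learn allocation when the last patient passes week 8, which is 44 weeks before that patient's week 52. Whether a patient needs rescue therapy is a judgement, and it is the only part of sustained remission observed after week 8. The partial Mayo score is listed without the adapted label that the article uses for versions omitting the physician's global assessment, so it appears to include that assessment. If the people making these judgements know the allocation, late comparisons between the arms can shift, in a direction that cannot be known in advance. The blinded committee reading sigmoidoscopy videos protects the endoscopic score, but not rescue decisions or symptom scores.

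**Working it through.** **The plan's own figure.** The exposure is expressed per 76 patients, so the sample size was checked first. Inputs from Sample size calculation: 10% versus 37%, two-sided α 0.05, power 80%. With the pooled-variance formula and mean rate 0.235:

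n = [1.960·√(2·0.235·0.765) + 0.842·√(0.10·0.90 + 0.37·0.63)]² / 0.27² = (1.175 + 0.478)² / 0.0729 ≈ 37.5, hence 38 per group and 76 in total. Power at 38 per group is 80.5%. The stated figure reproduces, and this point does not affect it.

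**Timing.** The gap from week 8 to week 52 is 44 weeks, or 308 days. If the last patient was included between 1 and 30 November 2024, week 8 falls between 27 December 2024 and 25 January 2025, and week 52 between 31 October and 29 November 2025. The article gives January 2026 as the end of follow-up, so at least 44 weeks of follow-up lie after the earliest permitted release.

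**Share of patients exposed.** Assumptions: uniform accrual, and de-blinding on the day the last patient reaches week 8. From mid-June 2020 to mid-November 2024 is 1614 days. A patient's visit at week w is still pending if the patient was enrolled within the last (w − 8) weeks of accrual.

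| Visit | Share pending at de-blinding | Of 76 |
|---|---|---|
| Week 18 | 70/1614 = 4.3% | 3.3 |
| Week 39 | 217/1614 = 13.4% | 10.2 |
| Week 52 | 308/1614 = 19.1% | 14.5 |

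Moving the start and end dates within the stated months gives an accrual period of 226 to 235 weeks and a week-52 share of 18.7% to 19.4%. That is 14.2 to 14.8 of 76, or about 19 of the maximum of 100. About 81% of patients would already have completed week 52. Since the exposed patients lose on average half of their 44 weeks to the de-blinded period, about 0.5 × 19% = 9.5% of all week 8 to 52 patient-time is affected.

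**Week-8 remitters exposed.** Only week-8 remitters can gain or lose sustained remission. At the planning rates, 38 × 0.10 + 38 × 0.37 = 3.8 + 14.1 = 17.9 patients remit. Of these, 17.9 × 0.191 ≈ 3.4 would still be awaiting week 52.

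**Sensitivity to the assumptions.** Faster accrual late in the trial would raise these numbers. A later de-blinding date would lower them.

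**The case against.** The strongest reply is that the article already calls treating physicians and visit staff blinded, releases only investigators, makes the release optional, and gives publication as its purpose. Patients may also be referred from other hospitals, so whoever prescribes rescue need not be an investigator. This stands in part. A reader might infer that rescue decisions will be made by unblinded physicians, but the text does not say so. What remains is that the release is a stated rule, the term investigators is not delimited, and nothing extends the blinding of treating and visit staff to week 52.

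A reader might also infer that sustained remission then rests on rescue decisions alone. It does not. It also requires clinical and endoscopic remission at week 8, and the trigger is all patients at week 8, so this release cannot touch those components.

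A third tempting reading is that a patient who relapses without receiving rescue would count as a sustained remitter. The condition is "no need for rescue therapy until week 52", and need is not the same as receipt. How need is judged is detail that an article may leave to the full protocol. Relapse is also captured by the later scores and by the Cox analysis of flares. Redefining the endpoint after recruitment has closed would be a preference with a credibility cost of its own, and it is not proposed here.

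Finally, unblinding for the open-label extension cannot affect sustained remission, because those patients have an endoscopic subscore of 2 or more and have already failed it. It can affect their later symptom scores.

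**Conclusion.** The point holds as a limited weakness in the blinding rule. The protocol permits investigators to be de-blinded before week-52 follow-up is complete, and does not say that those who treat and assess patients stay blinded. Under uniform accrual and the earliest permitted release, about 19% of patients (about 15 of 76) have week 52 pending, including about 3 to 4 week-8 remitters. The article gives neither the accrual pattern nor the date of any de-blinding, so these are estimates under assumption. The 44-week gap applies in full only to the last patient. The primary endpoint and the other week-8 outcomes are not affected. The documents do not show that bias has occurred or that any treating physician has been unblinded. The case for changing the rule is that it leaves tested secondary outcomes unprotected when protection is cheap.

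**What to change.** **Rule.** Limit the week-8 de-blinding to the team that analyses and reports the week-8 data. State that treating physicians, visit staff, outcome assessors and patients stay blinded to individual allocation until week 52, except for patients unblinded for the open-label extension.

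**If de-blinding has already taken place.** Report its date, who was unblinded, and which week 18, 39 and 52 assessments followed it. Add a sensitivity analysis restricted to assessments made before that date. For sustained remission, this means patients who had completed week 52 by then. Defining that subset by enrolment date, which is fixed before allocation, keeps the comparison a randomised one.

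**Cost.** Access control on the allocation list, and less freedom for investigators to see individual allocations when the week-8 results are published. No new assessments are needed, and neither the endpoint definitions nor the sample size changes.

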### Data collection

The assessments are summarised in online supplemental table 1 and a schematic overview of the interventions and assessments per timepoint is provided in figure 1. Patient data are handled with strict confidentiality and recorded in a pseudonymised format using unique participant codes. The code lists (ie, subject identification log) are digitally stored on a secure server hosted by the Amsterdam UMC and are only accessible to the principal investigator (PI) and project leaders. Data are saved in a secure online database (Castor, CIWIT BV, Amsterdam). All source documents and case report forms (CRFs) will be stored at the Amsterdam UMC for 15 years following the trial’s closure. All personnel involved in data entry receive appropriate training.

For patients who drop out of the study due to safety concerns (eg, worsening of disease), adjusted follow-up visits at similar timepoints (V10, T39, V11) will be conducted to collect safety data, including AEs and safety blood analysis at V11. If patients choose to withdraw from the study, no further follow-up data will be collected.

Videotaped sigmoidoscopies will be evaluated by a critical event committee (CEC), composed of two experienced IBD gastroenterologists, who will be blinded for randomisation allocation and the sequence of videos. Scoring will be conducted individually. In case of unequal scoring, videos will be reviewed together and discussed until consensus is reached.

### Statistical methods

Primary and secondary outcomes will be analysed using a ‘modified intention-to-treat’ design, meaning that data from all randomised patients will be analysed, with the exception of data of those who did not receive any FMT treatment (ie, patients who dropped out before V3). For the primary endpoint, the analysis will use a conservative approach in which participants with missing week 8 outcome data are classified as not in remission, irrespective of reason for missingness. To correct for missing data due to drop-outs, additional randomisation will be performed according to a fixed schedule outlined in online supplemental table 6.

Demographic data will be reported as either the mean with a 95% CI, or as the median and IQR for data not normally distributed. Analysis of the primary endpoint will be will be calculated using a two-sided χ^2^ test. Descriptive and exploratory data analysis will be reported as per the described primary and secondary endpoints. Statistical significance will be established at p<0.05 with a CI of 95%. P values of secondary outcomes will be adjusted using the Holm-Bonferroni procedure to account for multiple testing. Statistical analyses will be conducted using SPSS V.29.0 software (Chicago, IL) or R programming language version 4.

To identify dietary patterns assessed with the GINQ, principal component analyses will be performed on 22 food groups. Flare occurrence after FMT will be analysed using multivariable Cox proportional hazards models. To identify microbial candidates that are associated with response to FMT, we will perform differential abundance analysis comparing responders versus non-responders using linear regression analyses considering age, sex, BMI, proton pump inhibitor use, antibiotic and sequencing read depth as covariates. Next, we will analyse data derived from the longitudinal monitoring to detect changes after FMT and donor-derived engraftment of species associated with (non)-response.

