### Interventions

#### Faecal microbiota transplantation

Patients receive FMT weekly for 4 weeks (figure 1 and online supplemental table 1). Each treatment involves the administration of a 200 mL retention enema. The first and last treatments (week 0 and week 3) consist of dual-route administration, which includes nasoduodenal administration of 300 mL FMT via a CORTRAK* Enteral Access System (Avanos Medical, Alpharetta, USA) and a retention enema. To enhance engraftment, bowel lavage is performed with 3 L macrogol electrolytes solution (Moviprep) beforehand. Patients may choose to either drink the solution or administer it via the CORTRAK tube, which is then placed 1 day before the treatment (visit 2). We added this option to accommodate patients who have difficulty drinking the bowel lavage. In both cases, the bowel lavage is performed at home.

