### Harms

AEs will be monitored throughout the study. All AEs reported (spontaneously) by the patient, observed by the study team or communicated by other healthcare practitioners will be recorded. SAEs, as defined by the Centrale Commissie Mensgebonden Onderzoek (CCMO), are reported to the IRB within 15 days (or within 7 days if life-threatening). If SAEs are considered directly related to the FMT treatment, the DMSB will be notified within 24 hours. All AEs will be tracked until resolution or stabilisation. Follow-up of AEs may require additional tests, medical procedures and/or referrals to a general physician or medical specialist.

This study involves sigmoidoscopies with tissue sampling, CORTRAK placements and FMTs. The risks associated with these procedures are cited in the written patient information. Sigmoidoscopies with biopsies carry a small risk of complications, including bleeding and perforation.^39^ Feeding tube placements, including those with nasoduodenal tube positioning through a CORTRAK electromagnetic sensing device, involve a low risk of complications including aspiration, malpositioning and perforation.^40 41^ If there is any suspicion of tube malposition, a plain thoracic and/or abdominal X-ray will be performed. To prevent complications, sedation around the CORTRAK and FMT procedures is not allowed and patients with swallowing disorders will not be included in this study.

Prior studies have concluded that FMT is generally a safe therapy, with mostly transient AEs such as transient bloating, flatulence, abdominal pain and increase of stool frequency.^42^ SAEs are rare.^42^ Strict regulations apply for donor screening, minimising the risk of pathogen transmission (details on screening are listed in online supplemental tables 3 and 4 and online supplemental figure 1).

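### The modified ITT rule also covers adverse events, so a lavage or tube event that stops a randomised patient before any FMT falls outside the analysed AE outcome

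*Protocol article*

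**What the plan says.** All references are to the Protocol article.

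- **Secondary outcomes** ends its list with "Occurrence of AEs".
- **Statistical methods** opens with "Primary and secondary outcomes will be analysed using a" modified intention-to-treat design. It takes all randomised patients "with the exception of data of those who did not receive any FMT treatment (ie, patients who dropped out before V3"). It gives no exception for adverse events and names no safety set.
- **Faecal microbiota transplantation** requires lavage with 3 L of macrogol solution before the dual-route treatments. Patients may drink it or "administer it via the CORTRAK tube, which is then placed 1 day before the treatment (visit 2"). On location it says: "In both cases, the bowel lavage is performed at home".
- **Patient allocation and blinding** gives the order of events: "A research assistant conducts the randomisation and subsequently prepares autologous FMT or collects syringes with donor FMT".
- **Harms** says of tube placements that they "involve a low risk of complications including aspiration, malpositioning and perforation". It also says that AEs are monitored throughout the study.
- **Objective** names efficacy and safety together, for an FMT procedure that includes dual-route administration.

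**The concern.** A modified ITT set that leaves out never-treated patients can be defended for efficacy. Applied to adverse events in this trial, it makes inclusion depend on the outcome being measured. Part of the exposure comes before the first FMT: lavage for everyone, tube insertion the day before for some. A mild event in that window leaves the patient in the set. An event serious enough to end participation before V3 takes the patient out of both numerator and denominator.

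At stake is the absolute rate of procedural harm. The trial does not study a product given in isolation. Safety of the augmented procedure is a stated aim, and the introduction lists bowel cleansing together with the two routes among the measures meant to raise efficacy. A reader of the AE table would want to know how often the preparation itself caused harm, and the stated rule would leave out the cases in which that harm stopped the patient.

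**Working it through.** **Step 1. Does the rule reach adverse events?** AEs are a secondary outcome (Secondary outcomes). All secondary outcomes go into the modified ITT set (Statistical methods), and no exception is stated. So it does. This is a stated rule, not a silence.

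**Step 2. Can a randomised patient be exposed to a trial procedure and still be excluded?** Randomisation comes before product preparation (Patient allocation and blinding). The exclusion itself concerns randomised patients who left before V3, so randomisation precedes V3; the exact visit is not stated. The first lavage precedes the first FMT, and optional tube placement is at visit 2, one day earlier. So a patient can be randomised, have the procedure, suffer an event and leave before V3.

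**Step 3. The plan's own figure.** The article gives no AE rate and no count of drop-outs before V3. Its one relevant number is the planned 76 patients. With 10% versus 37%, two-sided α 0.05 and power 80%, the pooled-variance formula gives

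n = [1.960·√(2·0.235·0.765) + 0.842·√(0.10·0.90 + 0.37·0.63)]² / 0.27² = (1.175 + 0.478)² / 0.0729 ≈ 37.5, so 38 per group.

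The stated size reproduces (power at 38 per group: 80.5%). The AE analysis set does not affect it.

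**Step 4. Size of the understatement.** Let N be the number randomised, k the patients stopped before V3 by a procedural event, and m the treated patients with such an event. With every excluded patient counted in k:

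- rate in the modified ITT set = m / (N − k)
- rate in all randomised = (m + k) / N

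For m = 0 the gap is k/N. The values of k and m are assumptions, and intervals are exact (Clopper-Pearson).

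| N | k | m | Modified ITT | All randomised |
|---|---|---|---|---|
| 77 | 1 | 0 | 0/76 = 0% (upper limit 4.7%) | 1/77 = 1.3% (0.03% to 7.0%) |
| 78 | 2 | 0 | 0/76 = 0% (upper limit 4.7%) | 2/78 = 2.6% (0.3% to 9.0%) |
| 100 | 1 | 0 | 0/99 = 0% (upper limit 3.7%) | 1/100 = 1.0% (upper limit 5.4%) |
| 100 | 4 | 0 | 0/96 = 0% (upper limit 3.8%) | 4/100 = 4.0% (upper limit 9.9%) |
| 100 | 2 | 2 | 2/98 = 2.0% (upper limit 7.2%) | 4/100 = 4.0% (upper limit 9.9%) |

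The last row shows that when treated patients also have such events, the reported rate is no longer zero but is still too low. The value 100 is the article's maximum sample size.

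**Step 5. Would pooling everyone be better?** Not for events caused by FMT itself. If a of n treated patients have an FMT-related event and u untreated patients are added, the rate falls from a/n to a/(n + u). With n = 92 and u = 8 (assumed), it is multiplied by 92/100 = 0.92. The two kinds of harm therefore need different denominators.

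**The case against.** A safety set of patients who received at least one treatment is conventional, and the modified ITT set is in substance that set. The sentence in Statistical methods is followed by efficacy material (handling of missing week 8 data, replacement randomisation), so it may have been written with efficacy in mind. The full protocol or SAP, not shown, may define a safety set.

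Part of this stands. A treated-patient set is the right main set for FMT-related rates, as Step 5 shows. But the usual reasoning assumes that exposure starts with the first dose, and here lavage and tube placement come before it. What an unseen document might add does not alter what the article states, which is a rule that includes AEs.

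A reader might infer three stronger things that the documents do not support.

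- *That these harms vanish from the trial.* They do not. Harms says that all reported AEs are recorded and followed up and that SAEs go to the IRB. Data collection provides follow-up visits for patients who drop out for safety reasons. Monitoring gives the DSMB safety surveillance. These provisions govern collection and oversight; they do not change the analysed set, but nothing in them bars describing the events.
- *That the comparison between arms is biased.* Lavage and tube are the same in both arms and patients are blinded, so little such bias is expected.
- *That the AE rate is badly wrong.* Tube placement at visit 2 is optional, the event must also end participation before any FMT, and lavage and tube are used again at week 3. Procedural harms in treated patients therefore stay in the analysed outcome.

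**Conclusion.** The point holds in a limited form. As written, the AE outcome omits events from lavage or from visit 2 tube placement that stop a randomised patient before any FMT. The consequence is an understated absolute rate of procedural harm.

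The size cannot be fixed from the document, because neither the number of drop-outs before V3 nor a procedural event rate is given. It is probably small. One case in 77 would be 1.3% (0.03% to 7.0%) against a reported 0 of 76, and that contrast assumes no such event in any treated patient. The two intervals overlap heavily, so the figures illustrate the mechanism and do not estimate a bias.

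The conclusion rests on reading Secondary outcomes and Statistical methods literally, and on randomisation preceding the first lavage or tube placement, which the stated order of events supports without naming the visit. It does not extend to harms of the screening sigmoidoscopy. Eligibility depends on that examination, so a harm there that prevents randomisation would be missed by any set of randomised patients.

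**What to change.** In Statistical methods, limit the modified ITT rule to efficacy outcomes. Then state two things for safety:

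1. The main safety table gives AE rates in patients who received at least one FMT, so that FMT-related rates are not diluted by untreated patients.
2. A second table gives, by arm, all AEs and SAEs from randomisation to V3 in all randomised patients. Events are labelled by procedure (tube placement, lavage, other), and the denominator is everyone randomised.

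The cost is one sentence and one table. AEs are already recorded throughout the study, so no new data are needed. Recruitment is complete and follow-up runs to January 2026 (Trial status), so only the analysis changes. The sample size of 38 per group is unaffected. The downside is a slightly less favourable procedural AE rate.
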